**Inclusion criteria for healthy subjects**	
a. Those who have been proven to be healthy by physical examination and have no organic lesions or obvious functional diseases	
b. Age: 35 ~ 75 years old, male and female	
c. No cold, fever, cough, headache, and other physical abnormalities during the test	
d. Do not take any excitability drugs in the past 1 month, no recent treatment related to the trial content	
e. No history of mental or nervous system	
f. The subject agrees and signs the informed consent	

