### Study design

This clinical trial is designed as a double-blind RCT with 90 participants (60 stroke patients and 30 healthy controls) to be recruited. SPIRIT checklist and CONSORT statement were used when writing this study protocol [13, 14]. The whole study duration is about 17 weeks, including the washout period (7 days), the screening observation (3–7 days), the treatment period (3 weeks), and the follow-up period (3 months) (Fig. 1). After signing the informed consent (version date: 2021.11.19, version number: V1.1), all patients will be randomized divided into two groups in a blind manner—programmed flexor–extensor alternating electrical acupoint stimulation group (PES group) and conventional flexor–extensor alternating electrical acupoint stimulation group (CES group) with 30 cases in each, and the treatment will last for 3 weeks (6 days of treatment with 1-day rest per week). Healthy controls are used as a baseline without treatment. Participation in the trial is entirely voluntary, and they can withdraw at any time during the study without any reason. The participants are blinded, and the signal acquisition, evaluation, and outcome assessors are blinded. Because the treatment operation is too programmed, it is difficult to blind the performers. To prevent unblinding, subjects are advised not to discuss treatment options with evaluators (Figs. 2 and 3). All the patients will be followed up for 3 months. The follow-up time points will be at the end of the 1st month and 3rd month after the trial. The data and results will be monitored by the Data and Safety Monitoring Committee (DSMC) and the Ethics Committee.

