**Inclusion criteria for patients**	
a. Meet the diagnostic criteria of stroke [15, 16]	a. Severe cognitive dysfunction, severe aphasia, cannot cooperate with the whole treatment or testing process
b. Age: 35 ~ 75 years old, male and female	b. Patients with serious primary diseases such as heart, lung, kidney, liver, and endocrine system
c. Course of disease: 2 weeks to 3 months after stroke, stable vital signs, basically normal cognitive function, can cooperate to complete the test	c. Neurological or musculoskeletal diseases affecting functional recovery before onset
d. Manual muscle test (MMT) ≥ 2 [17], modified Ashworth (MAS) [18] of paralyzed upper limbs are graded I ~ II	d. Cerebral stem stroke or bilateral stroke
e. Body mass index (BMI) ≤ 28	e. Patients with severe anxiety, depression, affective disorders, schizophrenia, and other serious mental disorders
f. No serious heart, lung, kidney, and other functional damage; serious underlying diseases; pain in the affected side of the upper limb joint	f. Examination confirmed by brain tumor, brain trauma, brain parasitic diseases, metabolic disorders, rheumatic heart disease, coronary heart disease, and other heart diseases with atrial fibrillation caused by cerebral embolism
g. The informed consent is signed by the patient and/or his/her family members. Note: patients who meet the above 7 criteria can be included in this study	g. Patients with skin damage, infection, or deformity at the treatment site

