##### Healthy controls

Before the beginning of the whole clinical trial, the immediate alpha, beta, delta, and theta bands of the eyes-closed resting state EEG of the healthy controls in a quiet, without any interference laboratory will be recorded and ask them to do the “reaching and retrieving” gross movement, recording the real-time sEMG parameters (RMS and MF) of BB, TB, ECR, B, ED, and FCU during the whole process of the motion. The computer software calculates iEMG and MPF values.

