##### Sample size estimation

Sample size estimation was carried out according to the study objectives and protocol, and the difference between RMS values of sEMG of BB was obtained from the pretest of group 1 and group 2 after treatment and the healthy group. The difference between the healthy group and group 1 was 167.61 and 68.17 for group 2, and the standard deviations were respectively 127.22 and 148.46. The study effect size is 0.8, *α* = 0.05, test efficiency 1 − *β* = 0.80, and the number of sample groups is two. The sample size of each group is 25, and the total sample size is 50. Considering the possibility of sample loss in the trial, the sample size should be increased by 20%. Finally, the total sample size of this study should be 60 and divided into two groups with 30 sample size for each group.

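### Comparisons of patients with healthy subjects on the primary sEMG and EEG measures can be confounded: the BMI limit covers patients only, age and sex are not balanced, and the stated tests are unadjusted

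*Protocol article*

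**What the plan says.** The protocol article gives the healthy group a reference role in three places.

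- Study design plans for "90 participants (60 stroke patients and 30 healthy controls) to be recruited" and states: "Healthy controls are used as a baseline without treatment".
- Table 3 lists sEMG and EEG in healthy controls under the primary outcome.
- Sample size estimation uses planning figures that are distances from healthy: "the difference between RMS values of sEMG of BB was obtained from the pretest of group 1 and group 2 after treatment and the healthy" (that is, from the healthy subjects), namely 167.61 for group 1 and 68.17 for group 2.

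Table 1 defines the two populations separately. The age and sex item is the same in both lists: "b. Age: 35 ~ 75 years old, male and female". Patients must also satisfy "Body mass index (BMI) ≤ 28". The healthy list (items a to f) has no BMI item. Its general health condition is "Those who have been proven to be healthy by physical examination and have no organic lesions or obvious functional diseases", and it adds a drug condition: "Do not take any excitability drugs in the past 1 month". No quota or matching on age or sex is stated.

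Under Outcome measures, the healthy recordings are made "Before the beginning of the whole clinical trial". The Measurement section records age, gender and BMI in both populations. Data statistical analysis names one-way ANOVA with LSD, Welch's test with Dunnett's T3 for unequal variances, and the Mann–Whitney and Kruskal–Wallis tests. None of these uses a covariate.

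**The concern.** A reference group shows what stroke has changed only if it resembles the patients in other respects that affect the measurement. Here BMI is capped on one side only. The age and sex mix within a 40-year range is left to chance on both sides. The stated tests would then attribute any resulting difference to disease.

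The protocol does not say how strongly RMS or EEG band power depends on age, sex or BMI, so that dependence is an assumption of this point. The protocol does treat BMI as worth restricting in patients and worth recording in everyone.

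Two kinds of statement are at stake: a significance test of patients against healthy subjects, and any conclusion that one arm has come close to normal values. Because the planning figures are themselves distances from healthy, the report may well contain both.

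**Working it through.** **1. The plan's own figure.** Inputs from Sample size estimation: effect size 0.8, α = 0.05 (taken as two-sided), power 0.80. n per arm = 2 × (1.96 + 0.84)² / 0.8² = 2 × 7.84 / 0.64 = 24.5, rounded up to 25. The total is 50, and 50 × 1.2 = 60. The stated 25 and 60 are reproduced. The healthy group does not enter this calculation, and balancing it would not change the result.

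**2. Effect on comparisons of patients with healthy subjects.** Suppose there is no true stroke difference, but the healthy mean is displaced by k SD through age, sex or BMI. The two-sample t-test then has noncentrality k × √(n₁n₂ / (n₁ + n₂)). This is 3.87k for one arm against healthy (30 versus 30, 58 df) and 4.47k for both arms against healthy (60 versus 30, 88 df). The protocol gives no k, so a range is assumed. Probability of a significant result at a nominal 0.05:

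| Assumed spurious shift k (SD) | 30 versus 30 | 60 versus 30 |
|---|---|---|
| 0.1 | 0.07 | 0.07 |
| 0.2 | 0.12 | 0.14 |
| 0.3 | 0.21 | 0.26 |
| 0.5 | 0.48 | 0.60 |

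To put k on the RMS scale, pool the two planning SDs: √((127.22² + 148.46²)/2) = 138.25. A shift of 0.2 SD is then 0.2 × 138.25 = 27.65, and 0.5 SD is 69.13. The smaller planning gap to healthy, 68.17, is 68.17/138.25 = 0.49 SD. A displacement of that size in the right direction would by itself make the nearer arm look normal.

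**3. Effect on PES versus CES.** Let the healthy mean be displaced so that both gaps change by b, and assume both gaps have the same sign. The signed contrast is (167.61 + b) − (68.17 + b) = 99.44 for every b. In a simulation of 20,000 trials with 30/30/30 participants and no treatment difference, the PES versus CES type I error was 0.048 to 0.051 for healthy-mean shifts of 0 to 2 SD. That held both for LSD without a preliminary F test and for distances to the healthy mean. With LSD only after a significant overall F, the error ran from 0.025 to 0.051 over the same shifts, so it was not inflated beyond simulation error.

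**4. Why the healthy group should still stay out of that test.** There are only two patient arms, so the multi-group tests presumably include the healthy group; this is an inference. If so, its variance enters the pooled error. In the same simulation, with the healthy mean displaced by 1 SD, the PES versus CES type I error was 0.089 when the healthy SD was half the patients' SD. It was 0.021 when the healthy SD was 1.5 times theirs. The plan's Welch and Dunnett's T3 provision is meant for unequal variances. A direct two-arm test does not need it for this purpose.

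**The case against.** The strongest reply is that the trial asks whether PES does better than CES. That is answered by randomisation within one set of patient criteria, so the healthy group is background. This stands for the treatment contrast, as step 3 of the working shows.

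A reader might nevertheless infer that a misplaced reference could favour the wrong arm. With both gaps in the same direction, the ranking by closeness to healthy reverses only beyond (167.61 + 68.17)/2 = 117.89, or 0.85 SD, and only if absolute distance from healthy is the analysed quantity. The analysis section compares the measurements themselves and names no such endpoint, so the document does not support that reading.

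Other parts of the defence also stand:

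- The age range and the admission of both sexes are the same, and both lists exclude major disease. Only the distribution within those limits is uncontrolled.
- The one-month drug condition for healthy subjects is largely an inherent difference. All patients receive conventional medication after a recent stroke, so the asymmetry is not an error in itself.
- Recording healthy subjects first rules out matching them to individual enrolled patients, but not recruiting to age and sex quotas.
- Covariate adjustment might be specified in a full protocol or SAP that is not shown.

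The last reply is only partial. A later plan can add adjustment, but it cannot change the eligibility list that Table 1 fixes, and the tests the article does name are unadjusted.

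**Conclusion.** The point holds for comparisons of patients with healthy subjects and for statements that an arm has approached normal. As planned, these can be confounded by BMI, age and sex. The size is unknown: the 0.12 to 0.48 range (30 versus 30) rests on assumed shifts of 0.2 to 0.5 SD and a t-test at two-sided 0.05, and illustrates sensitivity rather than estimating a bias.

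A reader might go further and say that the baseline differs because of age, sex, body fat and drugs rather than because of stroke. The document gives neither size nor direction for any such shift, and stroke remains an obvious source of the difference. The supported statement is that the two sources cannot be separated by the planned tests. The estimate of PES against CES is unaffected.

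**What to change.** If healthy recordings are not complete, add the BMI ≤ 28 limit to the healthy list in Table 1 and recruit the 30 subjects to age-band and sex quotas that reflect the patient population. Trial status gives 3 June 2022 as the start of recruitment, and the healthy recordings were due before the trial, so they may already be finished. Repeating them would not be cheap and is not asked for here.

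In any case, change Data statistical analysis in two ways:

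- Report each comparison of patients with healthy subjects from a linear model with group, age, sex and BMI, in place of the unadjusted ANOVA. State that the comparison is non-randomised. All three covariates are already collected.
- Test PES against CES directly, with the healthy group left out of the model and its error term.

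The cost is slightly slower recruitment of older volunteers where recruitment is still open, and a little more analysis work. The number of participants and the recordings per person stay the same.

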### Interventions

All patients received conventional medication, rehabilitation, and acupuncture. As informed, during the study period, any other Chinese and Western medicine or treatment care related to this disease will not be permitted without the approval from the trial staff in advance.

### PES group

Based on the routine treatment in the department of acupuncture [17], the fourth generation of SZR-LF-2A low-frequency acupoint electric stimulation therapy instrument (patent No. ZL201610793646.9) jointly developed by our research group and the Robotics Institute of Harbin Institute of Technology will be used to improve the program (Fig. 4). The output of the improved instrument program is the patient should complete the motion of “reaching and retrieving,” namely, shoulder joint forward flexion—elbow extension—wrist dorsal extension—finger extension (“reaching for objects”), then grasping—wrist flexion—elbow flexion—shoulder joint backward extension (“retrieve objects”). All patients are in a sitting position, the wrist of the affected limb is suspended, and the other parts do not touch any plane. The electrode connection is divided into six groups, with two patches in each group, and acupoints on the affected side are selected. Power on after the connection and the current is within the patient’s tolerance, no pain. Acupoint selection is as follows (Table 2, Fig. 5).

**Fig. 4 Fig4:**
[figure not shown]
The fourth generation of the SZR-LF-2A low-frequency acupoint electric stimulation therapy instrument (patent no. ZL201610793646.9)

**Table 2 Tab2:** Acupoint selection

Joints	Flexor acupionts	Extensor acupionts
Shoulder	Jianqian^a^, Zhourong (SP 20)	Naoshu (SI 10), Tainzong (SI 11)
Elbow	Tianquan (PC 2), Quzhou point^b^	Naohui (SJ 13), Xiaoluo (SJ 12)
Elbow	Ximen (PC 4), Neiguan (PC 6)	Shousanli (LI 10), Waiguan (SJ 5)

^a^Jianqian: an extra point of the upper extremities

^b^Quzhou point (0.5 in. outside and 2 in. above Quze [PC 3], between the long and short heads of brachial biceps)

**Fig. 5 Fig5:**
[figure not shown]
Position of the flexor electrodes and extensor electrodes (photos are provided by one author of this article)

### CES group

Based on the conventional treatment in the Department of Acupuncture, the output mode of the fourth generation of low-frequency acupoint electric stimulation instrument of the original program will be adopted to synchronously stimulate the flexor and extensor acupoints respectively. The selection of acupoints, treatment time, and course will be the same as those of the PES group.

### Healthy control group

No treatment, as the baseline. Ask them to do the “reaching and retrieving” gross motion and record the resting state EEG and motion state sEMG parameters.

All the patients will receive free medical care during the study period, including counseling, therapy, electrophysiology, and scale evaluation. Participation in the trial is entirely voluntary, and patients can withdraw at any time during the study without any reason. The patient’s medical records will be kept in the hospital and only available to researchers, research authorities and ethics committee members of the Second Affiliated Hospital of Heilongjiang University of Chinese Medicine for review. Any public reporting of the results will not disclose the patients’ and healthy controls’ privacy. If the participant withdraws, their data will also be recorded but will not be used in this study.

Furthermore, for improving the adherence, the relevant staff will adequately explain the treatment method, duration, potential risks, and other details to the participants and keep connected whenever they need any medical service.

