### Measurement

*Patient demographics*: age, gender, BMI, course of disease, functional damage and serious underlying diseases, and date of admission.

*Healthy control demographics*: age, gender, BMI, once eyes-closed resting state EEG signals, and real-time sEMG signals.

*Treatment information*: enrollment time, treatment time, hospital discharge time, withdrawal time, problems in the treatment period, scale evaluation (MBI, CSS, FMA-U, MMT, and Brunnstrom), eyes-closed resting state EEG signals, and real-time sEMG signals [19].

*Follow-up*: dates of follow-up visit, adjuvant therapies, overall health status at and during follow-up (recovery condition of the upper limb, activity of daily living, fundamental diseases, drugs, death, loss of follow-up), and scale evaluation (MBI, CSS, FMA-U, MMT, and Brunnstrom). The follow-up staff will also be blinded.

The trial time enrollment schedule is estimated to be 6–8 months with a 3-month follow-up after the end of treatment. In 48 h after signing the informed consent, the patients will be randomly divided into groups according to the order in the clinic and then receive treatment after being evaluated (Table 3).

**Table 3 Tab3:** Schedule of study procedures

**Study period**	**Washout**	**Observation**	**Baseline**	**Treatment**			**Follow-up**	
Timepoint	≦7 days	3-7 days	0 day	1 day*	3 week◈	3 week^⊙^	1 month	3 month

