##### Management and safety monitoring

Before the initiation of this trial, the feasibility and innovation of this protocol have been discussed comprehensively in the seminar composed of five authoritative experts in the field. Then, the task will be divided, and the relevant personnel should receive training. To prevent treatment bias, all the staff including doctors, physiotherapists, group allocation workers, data collectors, data registers, and data processing analysts need to be trained in advance on the tasks they are responsible for. Participants are all anonymous in this trial, and their demographic information will be stored in a Word file with a password kept by the manager, and their trial data will be recorded in another Word file by relevant staff without any participants’ information. If there is any special circumstance, all trial personnel should be informed in advance, and approval should be obtained before checking the participants’ relevant records. The project manager, researchers, and experts from the Ethics Committee of the Second Affiliated Hospital of Heilongjiang University of Chinese Medicine are mainly responsible for the quality control of these trials.

In order to achieve the ability of standard operation procedure (SOP), filling in of case report form (CRF), Electronic Data Capture (EDC) system, and data entry. All data will be accurately double-entered into the EDC system, and the electronic CRF will be identical to the paper CRF. Moreover, multiple imputation will be used to deal with the missing data as part of the sensitivity analysis.

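### The rule that a withdrawn participant's data are not used removes randomised patients from the PES–CES comparison, and it does not fit the planned multiple imputation for those patients

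*Protocol article*

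**What the plan says.** The rule closes a paragraph in the Healthy control group subsection of Interventions: "If the participant withdraws, their data will also be recorded but will not be used in this study". Despite that heading, the paragraph is about the trial's patients. It covers their free care, their records and their freedom to leave: "patients can withdraw at any time during the study without any reason". The rule therefore reaches both randomised arms.

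Other parts of the article bear on it:

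- **Measurement** lists, as treatment information, "enrollment time, treatment time, hospital discharge time, withdrawal time, problems in the treatment period". Withdrawal after randomisation is thus foreseen and will be dated. Loss to follow-up is a separate item in the follow-up record.
- **Table 3 and Primary outcome measures** place the primary sEMG and EEG recordings before and after the first and last treatment. The scales continue to months 1 and 3, and adverse events are scheduled from day 1 to month 3.
- **Management and safety monitoring** says that "multiple imputation will be used to deal with the missing data as part of the sensitivity analysis", without saying which missing data are meant.
- **Sample size estimation** says: "Considering the possibility of sample loss in the trial, the sample size should be increased by 20" per cent, which takes 25 per group to 30.
- **Data statistical analysis** names the tests but not who is analysed. The article nowhere states an intention-to-treat or other analysis set.

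**The concern.** Randomisation makes the two arms comparable as allocated. Withdrawal comes later and may depend on tolerance of the stimulation, fatigue or poor recovery. The arms differ in stimulation output, and the operators know the allocation, so these reasons need not act equally in both. Once withdrawn patients are removed, the arms are no longer protected against such differences.

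The rule also discards usable information. A patient who leaves in week 2 has already given baseline and first-session primary recordings. A patient who completes treatment and withdraws in month 2 has given every primary recording, including week 3, and would still be left out. Read literally, the rule also covers adverse events, including those of a patient who left because of one.

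The planned imputation does not repair this. Imputing for a withdrawn patient needs that patient's recorded data, which the rule bars. As stated, the sensitivity analysis would not examine the effect of withdrawal.

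**Working it through.** **Inputs from Sample size estimation.** Effect size 0.8, alpha 0.05 (two-sided assumed), power 0.80. Pretest differences from the healthy group are 167.61 and 68.17, with SDs 127.22 and 148.46. There are 25 per group before and 30 per group after the loss allowance.

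**1. The plan's own sample size.** n per group = 2 × (1.96 + 0.8416)² / 0.8² = 15.70 / 0.64 = 24.5, so 25. Then 25 × 1.2 = 30 per group, 60 in total. The stated figures reproduce (normal approximation). The allowance covers 60 − 50 = 10 of 60 patients, or 16.7%.

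**2. Power if withdrawn patients are dropped.** Power = Φ(0.8 × √(n/2) − 1.96).

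| Analysed per arm | Power, normal | Power, t |
|---|---|---|
| 30 (all outcomes obtained) | 87% | 86% |
| 25 (16.7% lost) | 81% | 79% |
| 24 (20% lost) | 79% | 77% |

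The first row is an upper bound, because it supposes that every randomised patient has the outcome.

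**3. Bias if withdrawn patients are dropped.** Let w be the proportion withdrawn in an arm, and g the mean gap in outcome between those who stay and those who withdraw. The mean of those who stay differs from the mean of all randomised patients in that arm by w × g. With the same g in both arms:

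bias in the arm difference = (difference in w) × g.

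Scale: pooled SD = √((127.22² + 148.46²)/2) = 138.25, and pretest gap = 167.61 − 68.17 = 99.44. The withdrawal rates and g are assumptions. The formula gives a size; the direction depends on which arm loses more patients.

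| Withdrawal by arm (assumed) | g = 0.5 SD | g = 1 SD | Share of 99.44 |
|---|---|---|---|
| Any rates, g = 0 | – | – | 0 |
| Equal rates, same g | 0 | 0 | 0 |
| 3/30 v 7/30 (10 of 60 in all) | 0.133 × 69.1 = 9.2 | 0.133 × 138.25 = 18.4 | 9–19% |
| 3/30 v 9/30 (10% v 30%) | 0.20 × 69.1 = 13.8 | 0.20 × 138.25 = 27.65 | 14–28% |

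**4. Cross-check with another model.** Suppose there is no true effect, and withdrawal is driven by a normal liability correlated 0.3 to 0.5 with poor outcome. The spurious difference among those retained is 0.06 to 0.10 SD at 10% v 23%, and 0.09 to 0.15 SD at 10% v 30%. The latter is about 12 to 21 units, the same order as the table. It is zero when the correlation is zero or the rates are equal.

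**5. The two rules side by side.** One bars all data of a withdrawn patient. The other imputes missing data in a sensitivity analysis. For a patient who withdraws, imputation would start from data that may not be used. For a patient who misses a visit, has an unusable recording or is lost to follow-up without withdrawing, both rules can be followed.

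**The case against.** The sentence stands among remarks on voluntary participation, record access and privacy, not in the analysis section. It could be meant only for patients who withdraw consent to data use. Analysis sets are also commonly left to a fuller document, which is not shown. That is a fair account of how the sentence may have arisen, but the sentence names no consent condition. It is a rule the article states, not a detail it leaves out.

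The design also makes a large imbalance in withdrawal less likely. Both arms are active, with the same acupoints, treatment time and course. Patients are inpatients and blinded, and primary recordings end at week 3. This argues for modest figures. It does not justify a rule that removes the data needed to check.

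Four stronger readings are tempting but not supported:

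- *The two rules cannot both be followed.* They conflict only for withdrawn patients. Loss to follow-up is recorded separately, so imputation keeps a use.
- *The analysis is restricted to completers.* The rule excludes those who withdraw. It does not exclude non-adherent patients, those who miss visits or those lost to follow-up.
- *Adverse events of withdrawn patients will be lost.* The data are still recorded, and no passage says such events are left out of safety reporting. The wording is only broad enough to cover them.
- *The plan allows for 12 losses in 60.* Raising 50 by 20% allows for 10.

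**Conclusion.** The rule is wrong as written and should be changed. Followed literally, it removes randomised patients, even those with a complete week-3 primary outcome, for a reason arising after randomisation. It also leaves the planned imputation unable to address withdrawal.

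That the comparison loses the protection of randomisation follows from the text. The size of any bias does not: it runs from zero, with only the power loss shown above, to about 14 to 28 RMS units under 30% v 10% withdrawal and a gap of 0.5 to 1 SD. That case supposes 12 withdrawals in all, slightly more than the 10 the plan allows for. It also takes the pretest SDs as the spread of the outcome within each arm.

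**What to change.** Replace the sentence with wording such as: *All randomised patients are analysed in the group to which they were allocated; data collected up to withdrawal are used unless the patient withdraws consent to their use, and all recorded adverse events are reported.*

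Run the multiple imputation already planned on the full randomised set, so that it covers withdrawn patients. Present an analysis without withdrawn patients only as supportive.

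**Cost.** A short amendment and slightly more analysis work. The data are recorded in any case, and the sample size need not rise. Trial status gives recruitment from 3 June 2022 under consent version V1.1, so patients may already be enrolled, and using the data of those who withdrew may need ethics or consent-wording review. Inviting withdrawn patients to the already scheduled week-3 assessment would recover more outcomes, but it is optional and adds some effort.
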